**Removal, dropout, and termination criteria**
Noncompliance: patients who did not follow the trial design methods or who were unable to cooperate due to illness were excluded.Data completeness: this was removed if the data completeness was <80% or the treatment period was less than 6 weeks.Voluntary withdrawal: patients who voluntarily withdrew were lost to follow-up or received a kidney transplant.Adverse events (AEs): the study was terminated if serious AEs or disease deterioration occurred.

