### Sample Size Calculation

The sample size calculation formula for the multigroup mean is as follows:

$$n=\varphi^{2}\left(\sum_{i}s_{i}^{2}/g\right)/\left[\sum ({\bar{X}}_{l}-\bar{X}{)}^{2}/(g-1)\right]$$

where n represents the requisite sample size for each group, g represents the number of groups, and Si is the mean (SD) for each group. The values of φ are obtained from tables α, β, ν1, and ν2, with α=.05, β=.1, ν1=2, ν2=∞, and *φ*=2.52. A 2-sided test was used in this study, which stipulates that the test level α=.05, the test efficiency 1-β=.90, and the probability of a type II error is 0.10. The FRAIL scale score was used to calculate the effect size, and the average number of patients in each group, as previously described [37], was as follows: 3.29, 2.67, and 2.58, with SD values of 0.96, 0.87, and 1.02, respectively. These data were entered into the formula to calculate n=34. Considering the shedding rate of 10%, the actual required sample size for the 3 groups was estimated to be 38 per group, totaling 114 patients.

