### Intervention Measures

#### Control Group

The patient received conventional hemodialysis treatment and care without any additional interventions.

Conventional hemodialysis treatment is the standard dialysis treatment regimen that includes general symptomatic support, including the selection of appropriate dialysis machines, fluids, and methods; blood pressure and blood sugar management; correction of anemia; and prevention of secondary hyperparathyroidism.

Conventional hemodialysis care consists of 3 distinct phases. First, predialysis care was administered, where patients were introduced to the dialysis room environment, and assistance was provided in assuming a comfortable position. Dialysis machines were checked for readiness, general condition was evaluated, and predialysis weight was measured. Second, during dialysis care, we closely monitored vital signs, observed the vascular access for swelling or bleeding, ensured tight connections of external blood circuits, and responded to dialysis machine alarms. Third, postdialysis care included managing the vascular access, assessing postdialysis conditions, providing health education on diet, re-examination, and daily protection of vascular access.

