#### Intervention Schedule and Frequency

The integrated intervention protocol involved conducting sessions 3 times per week, with each session lasting 45 minutes. The duration was allocated as follows: 30 minutes for sitting Baduanjin exercises and 15 minutes for acupoint massage.

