#### Statistical Inference

Baseline characteristics were comparable across groups. Continuous variables were analyzed using one-way ANOVA (normally distributed data) or rank-sum test; categorical data were assessed with chi-square tests. Within-group pre-post comparisons used paired 2-tailed *t* tests (normal data) or rank-sum tests. Between-group differences postintervention were evaluated using one-way ANOVA (with least significant difference post hoc testing if significant) or rank-sum tests, as appropriate. Categorical outcomes were compared using chi-square tests.

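### Textbox 1 removes randomised patients for noncompliance, illness, under 6 weeks of treatment or under 80% data, which can bias the comparison, probably but not certainly towards the active arms

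*Protocol article*

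**What the plan says.** Textbox 1 of the protocol article has a block headed Removal, dropout, and termination criteria. Two of its entries matter here:

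- "Noncompliance: patients who did not follow the trial design methods or who were unable to cooperate due to illness were excluded"
- "Data completeness: this was removed if the data completeness was <80% or the treatment period was less than 6 weeks"

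The planned treatment lasts 8 weeks. A further entry in the block deals with safety: "Adverse events (AEs): the study was terminated if serious AEs or disease deterioration occurred".

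The Statistical Inference section gives the main comparison: "Between-group differences postintervention were evaluated using one-way ANOVA (with least significant difference post hoc testing if significant) or rank-sum tests, as appropriate". It does not name the patients who enter that comparison, and no other section returns removed patients to it.

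What patients are asked to do differs by arm. For control: "The patient received conventional hemodialysis treatment and care without any additional interventions". The massage arm has 15-minute sessions three times a week. For the combined arm: "The integrated intervention protocol involved conducting sessions 3 times per week, with each session lasting 45 minutes".

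**The concern.** Noncompliance, illness, early stopping and missing data all occur after randomisation and can depend on both the arm and the patient's course. If patients leave the analysis on these grounds, the groups compared are no longer the groups that were randomised.

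Two features of this trial make that more than a formality.

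- **Unequal exposure to the rules.** A control patient has no massage or Baduanjin session to miss. A patient in an active arm can fail the compliance rule by missing sessions. The same patient can fail the 6-week rule if sessions end early, for example after a pause that the investigator decides not to lift (Intervention Pause Criteria).
- **Overlap with the endpoint.** FRAIL scores fatigue, resistance, ambulation, illness and weight loss. Illness is itself a ground for exclusion in Textbox 1, and severe fatigue is among the reasons for stopping a session in Stage of Clinical Implementation. Patients who are removed may therefore be those with the worse primary outcome.

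At stake is the primary comparison. An active arm could look better because its poorer patients were taken out.

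**Working it through.** **Inputs from the documents (Sample Size Calculation).** FRAIL means 3.29, 2.67 and 2.58; SDs 0.96, 0.87 and 1.02; shedding rate 10%; 38 per group, 114 in total.

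**The plan's own figures.** The dropout step reproduces: 34 / (1 − 0.10) = 37.8, so 38 per group, and 3 × 38 = 114. The 34 itself does not follow from the stated formula, which gives 2.52² × 0.9063 / 0.1494 = 38.5. That is a separate matter and plays no part below.

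**Reference gap.** Highest minus lowest planning mean: 3.29 − 2.58 = 0.71. The section does not label the means by arm, so 0.71 serves only as a yardstick.

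**Assumptions (not in the documents).** A share f of one active arm is removed. Those patients would have scored d points worse than the patients kept. Control loses none. The lower f equals the plan's 10% shedding rate (about 4 of 38 patients); the upper, 20%, is double it. The upper d, 1.0, is one FRAIL item.

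**Formula.** Mean of all randomised in the arm = mean of those kept + f × d. Removal therefore shifts the arm's mean by −f × d; lower FRAIL is better.

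| f | d | Shift | Share of 0.71 |
|---|---|---|---|
| 10% | 0.5 | −0.05 | 7% |
| 10% | 1.0 | −0.10 | 14% |
| 20% | 0.5 | −0.10 | 14% |
| 20% | 1.0 | −0.20 | 28% |

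**Dependence on which arm loses patients.** A simulation used 38 per arm, no true treatment effect, d = 1 and SD √0.9063 = 0.952, where 0.9063 = (0.96² + 0.87² + 1.02²) / 3. Every arm held the same share of poor-outcome patients; only their removal differed. Each cell gives the combined-minus-control difference, then the one-way ANOVA type I error at nominal 0.05.

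| Poor-outcome share | Both active arms only | All arms equally | Control only |
|---|---|---|---|
| 10% | −0.10; 0.07 | about 0; 0.05 | +0.10; 0.07 |
| 20% | −0.20; 0.14 | about 0; 0.05 | +0.20; 0.13 |
| 30% | −0.30; 0.26 | about 0; 0.05 | +0.30; 0.21 |

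With all patients kept, the difference is about 0 and the type I error about 0.05. If those removed from the active arms do one point better rather than worse (10% share), the difference is about +0.10, against those arms.

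**The case against.** **The article is condensed.** Analysis sets and missing-data methods may be set out in a full protocol or SAP that is not shown. Evaluation Indicators also requires follow-up data after 8 weeks, and Textbox 1 does not say that assessment ends on removal. Silence on analysis sets would indeed be no finding. But the removal rules are stated text: a SAP that analysed all randomised patients would contradict them as written, so they need changing either way.

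**The direction is not established.** A reader might infer that the rules certainly favour the active arms. The documents do not support that. The illness and 80% rules apply in every arm. Table 2 places control-group routine care in the 8-week intervention column, so the 6-week rule could be read as covering control too. Nothing states that those who stop are the frailest; fitter, less motivated patients may also stop. This part of the objection stands: the direction is probable, because only the active arms have sessions to fail, but removals from control could offset or reverse it.

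**Deterioration is not a stated removal ground.** A reader might infer that patients who deteriorate are also deleted. The text says only that "the study was terminated if serious AEs or disease deterioration occurred". It does not say that their data are dropped. What is explicit is exclusion for illness that prevents cooperation.

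**The two active arms against each other.** A reader might set the 0.20 shift against the 0.09 gap between the two lower means (2.67 − 2.58) and conclude that the bias could be 2.2 times that gap. That needs a 20% loss from one active arm and none from the other, although both have sessions to fail. The net shift is the difference between the two arms' shifts: zero if equal, and 0.05 to 0.10 for 10% against 20% with the same d. The means are also not assigned to arms. That ratio should not be used.

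**Conclusion.** The defect holds in this form: Textbox 1 excludes or removes randomised patients for noncompliance, illness that prevents cooperation, under 6 weeks of treatment or under 80% data, and nothing limits these rules to a secondary analysis. Followed as written, they break the randomised comparison for the primary endpoint and can bias it, probably but not certainly towards the active arms.

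The size is illustrative: 0.05 to 0.20 FRAIL points, or 7% to 28% of 0.71. It rests on the assumed removal shares and outcome gap, and on no removal from control. At the plan's own 10% rate the range is 0.05 to 0.10 points, or 7% to 14%. With equal removal of similar patients it is about zero. The need to amend the rules does not depend on the direction or the exact size. It should be settled before the effect analysis, which the article says has not yet been done; 52 of 114 patients were enrolled as of August 2025.

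**What to change.** - Make the primary analysis all randomised patients in their allocated arm.
- Collect week-8 FRAIL from everyone still consenting, including those who stop the sessions.
- Handle the remaining missing values with a prespecified method; multiple imputation is one suitable choice.
- Keep the noncompliance, 6-week and 80% rules only to define a per-protocol sensitivity set.
- State whether data from patients terminated for serious AEs or deterioration are analysed. This concerns the data only and changes no clinical stopping rule.

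The cost is an amendment, some extra week-8 assessments and possibly a smaller estimated effect. Eligibility requires dialysis three times a week, so most patients who stop the sessions can still be assessed when they attend. The planned total of 114 does not change on this account.

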### Sample Size Calculation

The sample size calculation formula for the multigroup mean is as follows:

$$n=\varphi^{2}\left(\sum_{i}s_{i}^{2}/g\right)/\left[\sum ({\bar{X}}_{l}-\bar{X}{)}^{2}/(g-1)\right]$$

where n represents the requisite sample size for each group, g represents the number of groups, and Si is the mean (SD) for each group. The values of φ are obtained from tables α, β, ν1, and ν2, with α=.05, β=.1, ν1=2, ν2=∞, and *φ*=2.52. A 2-sided test was used in this study, which stipulates that the test level α=.05, the test efficiency 1-β=.90, and the probability of a type II error is 0.10. The FRAIL scale score was used to calculate the effect size, and the average number of patients in each group, as previously described [37], was as follows: 3.29, 2.67, and 2.58, with SD values of 0.96, 0.87, and 1.02, respectively. These data were entered into the formula to calculate n=34. Considering the shedding rate of 10%, the actual required sample size for the 3 groups was estimated to be 38 per group, totaling 114 patients.

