**Inclusion criteria**
Age: 45‐75 years with end-stage renal disease (uremia stage).Dialysis duration: receiving hemodialysis treatment ≥3 months, 3 times a week, and 4 hours per session, with stable vital signs.Frailty status: evaluated using the FRAIL (Fatigue, Resistance, Ambulation, Illness, and Weight Loss) scale, with scores of ≥1 indicating prefrailty or frailty.Cognitive and communication ability: clear consciousness, normal hearing, and ability to communicate normally.Physical function: no physical activity disorders, no regular exercise, able to understand and follow demonstration actions.Acupoint skin condition: intact skin at acupoint massage sites.Voluntary participation: willing to participate in the study.

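### The printed sample-size formula and inputs give 39 evaluable patients per group, not 34, so 114 patients deliver about 85% power after the planned 10% dropout, not 90%.

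*Protocol article*

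**What the plan says.** The Sample Size Calculation section sets n per group equal to φ² times the mean of the group variances, divided by the sum of squared deviations of the group means from the grand mean over g−1. It takes φ=2.52 from a table entered "with α=.05, β=.1, ν1=2, ν2" infinite. The design targets are explicit. The section declares a two-sided procedure, "which stipulates that the test level α=.05, the test efficiency 1-β=.90". It gives the corresponding beta as 0.10.

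The planning values are FRAIL scores from a cited study. The section says the average in each group "was as follows: 3.29, 2.67, and 2.58, with SD values of 0.96, 0.87, and 1.02, respectively". It continues: "These data were entered into the formula to calculate n=34". After allowing for 10% loss, "the actual required sample size for the 3 groups was estimated to be 38 per group, totaling 114 patients". The total of 114 recurs in the abstract and in the Participants and Random Allocation Method sections.

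**The concern.** The section prints everything needed to repeat the calculation, and repeating it does not return the printed answer. This is the only justification given for the size of the trial, and it concerns the primary outcome. If the result is wrong while the inputs stand, the trial does not have the power it claims, and a null finding would be judged against a type II error that is too small. Loss from the analysis is also to be expected: Textbox 1 provides for removing patients for noncompliance, incomplete data or a short treatment period. The dropout allowance therefore has to be real.

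**Working it through.** **Inputs, all from the Sample Size Calculation section.** φ=2.52; g=3; means 3.29, 2.67, 2.58; SDs 0.96, 0.87, 1.02; dropout 10%; stated n=34, raised to 38 per group.

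**Step 1. Attempt to reproduce n=34.**
- Mean variance: (0.9216 + 0.7569 + 1.0404)/3 = 0.9063.
- Grand mean: (3.29 + 2.67 + 2.58)/3 = 2.8467.
- Sum of squared deviations: 0.4433² + 0.1767² + 0.2667² = 0.29887. Divided by g−1 = 2, this is 0.14943.
- φ² = 2.52² = 6.3504.
- n = 6.3504 × 0.9063 / 0.14943 = 38.51, rounded up to **39**. The stated 34 is not reproduced; it is 5 per group too low.

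**Step 2. Is the table value right?** With α=0.05, numerator df 2 and infinite denominator df, 90% power needs a noncentrality of 12.654, so φ = √(12.654/2) = 2.515. The printed 2.52 is correct.

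**Step 3. What φ would give 34?** For exactly 34, φ = √(34 × 0.14943/0.9063) = 2.37. For anything above 33 that rounds up to 34, φ must exceed √(33 × 0.14943/0.9063) = 2.33. Neither agrees with 2.52.

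**Step 4. Other ways of using the same inputs.**

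| Variant | n per group |
|---|---|
| Grand mean rounded to 2.85 | 38.5 |
| Square of the mean SD | 38.4 |
| Smallest SD throughout | 32.2 |
| Largest SD throughout | 44.2 |
| Divisor g instead of g−1 | 57.8 |
| Exact noncentral F, 90% power | 40 |
| Two-group formula, highest mean against each of the others, unadjusted | 41 and 46 |

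None gives 34.

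**Step 5. Dropout.** The inflation step itself is sound: 34/0.9 = 37.8, so 38. Applied to 39 it gives 39/0.9 = 43.3, so 44 per group and 3 × 44 = 132. The planned 38 is slightly below the 38.5 that the formula requires before any dropout.

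**Step 6. Power of the planned trial.** One-way ANOVA, noncentral F with df 2 and 3(n−1), and noncentrality n × 0.29887/0.9063:

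| Evaluable per group | Noncentrality | Power |
|---|---|---|
| 34 (38 × 0.9 = 34.2) | 11.21 | 84.8% |
| 38 (no dropout) | 12.53 | 88.8% |
| 39 | 12.86 | 89.7% |
| 40 | 13.19 | 90.5% |

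A simulation with normal data and the three unequal SDs gives 84.4% at 34 and 88.5% at 38, so averaging the variances does not drive the result. The formula's 39 falls just short of 90% here because the table value assumes infinite denominator df; with the actual df, 40 are needed.

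**The case against.** The best objection concerns the diagnosis. The arithmetic shows that the formula, inputs and result disagree, but not which of them is wrong. A correct φ does not rule out a misprinted mean or SD: the planning values come from a cited study that is not at hand, and the sentence introducing them is itself garbled. A reader might infer that the slip must lie in the substitution. That is the simplest explanation, but the document does not establish it. This part of the objection stands, and the repair has to begin with reconciliation.

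A second objection is that the shortfall is modest: about 1 point with no dropout and about 5 points at the planned loss. The Discussion also already concedes a small sample. The size is fairly put, and the type I error and design are unaffected. But the concession in the Discussion does not correct the stated 90%.

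A reader might go further and infer that true power is far below 85%, because eligibility admits patients "with scores of ≥1 indicating prefrailty or frailty" while one planning mean, 3.29, lies in the frail range. The document does not support this. The three means are not labelled by arm. The prevalences in the Background come from different studies and are not said to be based on the FRAIL scale. The eligibility floor does not fix the mix of patients enrolled. Any lower power figure would need an invented control mean and an invented rule for how the SD behaves.

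**Conclusion.** The point holds. On the values as printed, the requirement is 39 evaluable per group, not 34, and 114 patients contain no dropout allowance. Power for the overall three-group test is about 85% after 10% loss (type II error about 0.15, one and a half times the stated 0.10) and about 89% if nobody is lost.

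These figures rest on the printed means and SDs being the intended ones, on approximate normality, and on the one-way ANOVA of postintervention scores named under Statistical Inference. They do not show that the planning values are implausible. Nor can it be said that adjusting for baseline would restore 90% at this size: that depends on the correlation between baseline and week-8 scores, which the document does not give.

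**What to change.** Check the printed means and SDs against the cited source and reconcile them with the formula and with n=34. If a misprint is found, correct it and show that the formula then returns the stated n. If not, replace 34 with 39 and state that 114 patients give about 85% power after 10% dropout and about 89% with none, with a type II error of about 0.15 in place of 0.10.

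This costs one corrected paragraph and a less favourable power statement; no additional patients are needed. Keeping the 90% claim through sample size instead would take 44 per group under the protocol's own rule, 132 − 114 = 18 more patients. Enrolment was reported at 52, with the analysis of effects still to come, so the figure can be corrected before any result is interpreted against it.

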### Random Allocation Method

A randomized controlled trial design was used in this study, whereby participants were randomly allocated to the experimental and control groups. After generating the random numbers using SPSS 25.0 with the initial seed value 120983, the allocation sequence (Group A for participants 1‐38, Group B for 39‐76, and Group C for 77‐114) was concealed using sequentially numbered, opaque, sealed envelopes. These envelopes were prepared by an independent statistician not involved in participant recruitment or assessment. Each envelope contained the group assignment for the corresponding participant and was only opened by the research coordinator after a participant had completed enrollment procedures, ensuring that neither the participants nor the recruiting researchers could predict or influence group allocation. This procedure was implemented to minimize the risk of selection bias.

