##### Intervention Method

Before enrollment, the research team provided patients with a comprehensive introduction to the acupoints for pressing, including their functions and associated precautions. This ensured patient acceptance and cooperation. The acupoint pressing procedure was performed by trained members of the research team. Patients were reminded of the specific locations and functions of the acupoints during the procedure. The applied pressure was carefully adjusted to remain within the tolerance levels of the patients.

The force was applied uniformly and gently to prevent skin damage. The patient’s subjective sensations were closely monitored throughout the procedure, and the patients were observed for any signs of injury, erythema, or edema on the skin. To avoid discomfort, massage should be avoided when the patient experiences anxiety, hunger, or over-satiation.

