## Results

This study was funded in December 2024, with data collection officially initiating on December 15, 2024, and projected to conclude in November 2025. As of the article submission date, 52 participants have been successfully enrolled, and all planned interventions are ongoing. Preliminary analysis of baseline demographic characteristics (eg, age, gender, dialysis duration) has been completed, confirming the balance of key variables across the 3 study groups, while full statistical analysis of intervention effects will be conducted immediately after the completion of all participant interventions and data collection. The trial is expected to be fully completed within 2025, with final study results anticipated to be published in Spring 2026.

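### The stated allocation sequence is three consecutive runs of participant numbers, which contradicts random, unpredictable allocation and the three-group balance reported at 52 enrolled

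*Protocol article*

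**What the plan says.** All references are to the protocol article.

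- **Random Allocation Method**, source of randomness: "After generating the random numbers using SPSS 25.0 with the initial seed value 120983".
- **Same section**, the sequence: "the allocation sequence (Group A for participants 1‐38, Group B for 39‐76, and Group C for 77‐114". It "was concealed using sequentially numbered, opaque, sealed envelopes".
- **Same section**, link to the patient: "Each envelope contained the group assignment for the corresponding participant". The envelope is opened once enrolment procedures are complete.
- **Same section**, the assurance given: "ensuring that neither the participants nor the recruiting researchers could predict or influence group allocation".
- **Results**: "As of the article submission date, 52 participants have been successfully enrolled". The abstract dates that count to August 2025. The same paragraph of Results reports a completed baseline analysis "confirming the balance of key variables across the 3 study groups".
- **Acupoint Massage Group, Intervention Method**: "Before enrollment, the research team provided patients with a comprehensive introduction to the acupoints for pressing".

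The section does not say that the random numbers were ranked or sorted, or that the three ranges are anything other than participant numbers.

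**The concern.** The section names a seeded random-number generator, then states a sequence in which the random numbers play no visible part. Envelope 1 belongs to participant 1, and participants 1 to 38 all go to A. Anyone who knows the rule knows every assignment in advance.

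Two things are at stake.

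- **Selection bias.** The trial is single-centre, and the Blinding section accepts that patients and operators know the arm. The section on the primary indicator concedes that the FRAIL scale lacks objective indicators. The between-group test described under Statistical Inference is a post-intervention ANOVA or rank-sum test with no baseline adjustment mentioned. Any selective enrolment would therefore pass directly into the main comparison.
- **Confounding with calendar time.** If arms were filled one after another, the comparison between arms would also be a comparison between recruitment periods.

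The Conclusions present random allocation and concealed grouping as strengths, so readers will rely on this section.

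**Working it through.** **Inputs.** Ranges 1–38, 39–76 and 77–114, and seed 120983 (Random Allocation Method). 38 per group, 114 in total (Sample Size Calculation). 52 enrolled by August 2025 (abstract and Results). First participant on 8 August 2024 (abstract); data collection from 15 December 2024 (Results).

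**1. The ranges match the planned sizes.** Each range holds 38 numbers, and 3 × 38 = 114. The ranges are complete and equal; the problem is their order.

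**2. Reading A: the ranges are enrolment numbers.** At 52 enrolled:
- A = 38
- B = 52 − 38 = 14
- C = 0

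The remaining 114 − 52 = 62 assignments would be 38 − 14 = 24 to B, then 38 to C, all known in advance. With C empty, balance over three groups could not have been checked. Random Allocation Method, read this way, and Results cannot both be true.

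**3. Reading B: the ranges are cut-points on ranked random numbers.** This gives a random permutation of 38 A, 38 B and 38 C. At 52 enrolled:
- Expected count per arm: 52 × 38/114 = 17.3. In a simulation of 10,000 permutations, the 95% range for one arm was 12 to 22.
- Probability that C is empty: C(76,52)/C(114,52) ≈ 3.8 × 10⁻¹⁴.

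Results therefore fits reading B and not reading A. The arm counts at 52 would distinguish the two almost with certainty.

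**4. Calendar time, reading A only.** The two start dates, and taking the count at the start or end of August 2025, give about 52/12.75 = 4.1 to 52/7.5 = 6.9 patients per month. Each arm would then fill a separate window of about 38/6.9 = 5.5 to 38/4.1 = 9.3 months.

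**5. Concealment, reading B only.** 62 of 114, or 54%, were still to be enrolled when the text was written. It prints four parts of the recipe: software, version, seed and cut-points. It does not give the type of generator, the distribution drawn from, the case order, the ranking direction or which arm each letter denotes. Site staff know the arms of patients already treated, so candidate reconstructions could be checked against up to 52 known assignments.

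For scale, the same simulation gives the success of someone who sees past allocations but has no list and always guesses the arm with most places left. That person is right for about 44% of the last 62. A reconstructed list would raise this to 100%. No reconstruction was attempted.

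**6. Order of briefing and envelope.** Intervention Method puts the acupoint introduction before enrolment; Random Allocation Method opens the envelope after it. If the introduction is specific to the massage arm, the arm would have to be known before the envelope was opened. If every candidate receives it, there is no conflict.

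**The case against.** The strongest reply is that the trial was probably randomised and only badly described. A seed serves no purpose if the first 38 envelopes all hold A, and the three-group balance at 52 enrolled is what a ranked permutation would produce. This stands as a reason not to conclude that allocation was non-random. It does not rescue the section: its wording ties the ranges to participant numbers and the envelopes to the corresponding participant, so what it states is a wrong rule and not merely an abbreviated one.

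A reader might also infer that all 62 remaining assignments can be reproduced from the article. The documents do not support that, because several elements of the recipe are missing. Nor do they give a publication date. Data collection was projected to end in November 2025, so release of the seed during recruitment is plausible but not documented. And a seed printed later does not undo concealment for those already allocated from sealed envelopes prepared by an independent statistician.

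Finally, the acupoint introduction may be consent-stage information for every candidate. It is not evidence that recruiters knew the arm, and only the order of events needs clarifying.

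**Conclusion.** The point holds as a contradiction in the stated rule. As written, the sequence is deterministic, conflicts with the claim of unpredictability, and gives 38/14/0 at 52 enrolled, against a report of balance over three groups. This needs only the ranges and the enrolment count, and confidence in it is high.

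Which reading is true cannot be settled from the documents. The baseline report favours ranked random numbers, so the inference that the trial is not randomised goes too far. On that reading there remains a weakness of concealment, affecting at most the 62 (54%) not yet enrolled at submission. Its practical effect depends on two things not shown: that the list can be regenerated, and that the seed was released while recruitment was open. The separate recruitment windows of 5.5 to 9.3 months apply only if enrolment order was followed.

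The correction must be made, because every between-group claim rests on this section.

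**What to change.** **In all cases.** Rewrite Random Allocation Method to state how the random numbers were mapped to groups and whether the ranges are ranks or enrolment numbers. Report the arm counts among the first 52.

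**If allocation followed enrolment order.** Report those participants as non-randomised, and have the independent statistician issue a properly random, concealed list for the rest. Spread equally over three arms, 62 patients give about 62/3 = 20.7 per arm against the planned 38. The sponsor would have to extend recruitment or accept a smaller randomised comparison.

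**If allocation was rank-based.** Do not disclose the seed while recruitment is open. If it has already been disclosed, have the independent statistician regenerate the remaining list with an undisclosed seed, in new envelopes, keeping the planned arm totals. For example, counts of 17/17/18 at the change would leave 21/21/20 to allocate. Add a sensitivity analysis by recruitment phase, before and after the new list.

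**Secondary.** Reconcile the timing of the acupoint introduction with the opening of the envelope: either say that every candidate receives it, or place it after allocation.

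**Cost.** If rank-based: a corrected paragraph, a table of counts and, if needed, a new list, a short amendment and one extra term in a sensitivity analysis. If enrolment order was followed, the cost is the loss of the first 52 from the randomised comparison.
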